### Sample size and data collection approach

Limited evidence from previous descriptive studies discussed above suggests a difference in SBR from 3 to 35% between a FBH^+^ and a FPH method [19,20]. A difference of at least 15% between the two methods could be sufficient to consider a major change in the DHS core questionnaire. Since this is the first direct comparisons of the two methodologies, we powered the randomized comparison to capture a 15% difference assuming that a difference less than 15% will not justify a change in survey methodology (see Appendix S1 in **Online Supplementary Document**).

Based on the recorded SBR and total births per HDSS over the last three years, the overall SBR for the final sample of births captured in the survey is expected to be around 28.4 per 1000 total births, if all women are surveyed. However, we needed to account for possible outmigration, unavailability of women at any visit, or non-consent. After adjusting for these factors, we expect the SBR for the FPH arm to be around 26.7 per 1000 total births (see Appendix S3, Table S2.2 in **Online Supplementary Document** for details). Assuming a SBR of 26.7 per 1000 total births in the FPH arm, a total sample size of at least 68 000 births would be required across the five sites to have 80% power to detect a difference of 15% or more between the proportion of total births that are stillbirths in the FBH^+^ and the FPH at the 5% significance level (alpha = 0.05), including a small design effect (DEFF = 1.1), as stillbirths may be clustered in individual women. The lower the SBR captured in the FBH^+^ arm, the higher the sample size will be required to detect 15% difference between the two arms (see **Table 3**).

**Table 3 T3:** Required sample size by stillbirth rate (SBR) for the household survey randomised comparison, assuming alpha = 0.05 and an expected 15% difference in SBR*

Assumed SBR in birth history group/ 1000 total births	Predicted SBR in pregnancy history group/ 1000 total births	Number of total births to achieve 80% power	Sample size - number of births required including design effect and non-response (15%)
23.00	26.45	63 604	80 459
23.20	**26.70**	**62 348**	**68 583**
24.00	27.60	60 886	77 021
25.00	28.75	58 386	73 858
26.00	29.90	56 078	70 939
27.00	31.05	53 942	68 237
28.00	32.20	51 958	65 727

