### Analysis by objective

The overview of research objectives, main research questions, and analytical approaches are summarised in **Table 1**. For all study objectives, the primarily analyses will be performed overall across countries (as pooled analyses), and comparative secondary analyses will be performed by site separately, whenever possible. Data will be cleaned according to an agreed protocol, including logical and completeness checks. Quantitative analyses will be undertaken with Stata 15SE (Stata Statistical Software: Release 15. College Station, TX: StataCorp LLC). Qualitative analyses will be conducted using NVivo software (NVivo qualitative data analysis Software; QSR International Pty Ltd Version 12, 2018).

#### Objective 1

A population-level descriptive analysis will be conducted comparing SBR and NMR by FBH^+^ or FPH, and by maternal characteristics (age, parity, residence, and education status). Crude risk ratios with its 95% confidence interval will be computed for comparison of SBR and NMR between FBH^+^ and FPH overall and by study site using the meta-analysis methods with Random Effects. Regression models will be fitted to assess determinants of adverse pregnancy outcomes using Generalised Estimation Equations to adjust for clustering of stillbirths or neonatal deaths within the same woman, therefore taking into account design effect. We will use paradata to assess differences in average time taken to complete the FBH^+^ and FPH.

#### Objective 2

We will undertake descriptive analyses of selected indicators including fertility intentions, selected pregnancy outcomes (TOP, miscarriage, birthweight, gestational age), as well as birth and death registration. This will include estimates of frequency of reported TOP and miscarriage, coverage of reported birthweight, gestational age, birth and death certification, and of fertility intentions. The answerability of new/refined questions will be assessed by describing patterns of non-response and heaping, where appropriate. Variation in these indicators by pregnancy outcome, maternal or interviewer characteristics will be assessed. For gestational age, internal consistency in the survey will be assessed by comparing women’s reporting of gestation in months compared to weeks, and reported maternal perception of the birth to be preterm. Survey paradata will also be analysed to assess time taken to complete and frequency of repeated corrections to relevant survey questions.

#### Objective 3

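### The 80% power belongs to a single pooled two-proportion test, but the only method named for the overall stillbirth risk ratio is a five-site random-effects meta-analysis, which has about 71% power even with no heterogeneity

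*Protocol article*

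**What the plan says.** Sample size and data collection approach: about 68 000 births across five sites are to give "80% power to detect a difference of 15% or more between the proportion of total births that are stillbirths" in the two arms, "at the 5% significance level (alpha = 0.05"), "including a small design effect (DEFF = 1.1"). The article explains the design effect by stillbirths clustering in individual women. The bold row of Table 3 sets 23.2 per 1000 in the FBH+ arm against 26.7 in the FPH arm, and gives 62 348 births before inflation and 68 583 after.

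Analysis by objective, opening paragraph: "the primarily analyses will be performed overall across countries (as pooled analyses"), with site-by-site comparisons secondary.

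Analysis by objective, Objective 1: crude risk ratios for SBR and NMR between the arms are computed "overall and by study site using the meta-analysis methods with Random Effects". Table 1 also lists meta-analysis for this comparison. Generalised estimating equations appear only for models of the determinants of adverse outcomes, not for the contrast between arms.

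The article names no between-site variance estimator and gives no expected heterogeneity. The Discussion repeats that the study is powered for a 15% difference.

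**The concern.** A pooled test treats all births as one two-arm comparison. A random-effects meta-analysis adds an estimated between-site variance to each site's sampling variance. With five sites that variance rests on 4 degrees of freedom and often comes out above zero by chance, which widens the interval even when every site has the same effect. If the effects do differ, precision is limited by the number of sites, and more births help little.

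The 15% difference is the article's own threshold for considering a major change to the DHS core questionnaire. If the random-effects summary is the primary result, a true gain of that size would be declared non-significant more often than the stated 20% of the time.

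**Working it through.** **Inputs from the article.** Two-sided alpha 0.05 (sidedness is assumed, but it reproduces the stated figure); 80% power; p1 = 0.0232 (FBH+) and p2 = 0.0267 (FPH); design effect 1.1; expected births from Table 2: Bandim 17 000, Matlab 21 000, Kintampo 14 500, Dabat 5700, IgangaMayuge 9800, total 68 000. Allocation 1:1 is assumed; it also reproduces the stated figure.

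**Step 1: the article's own number.** With p̄ = 0.02495,

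n per arm = [1.960·√(2p̄(1−p̄)) + 0.8416·√(p1(1−p1) + p2(1−p2))]² / (p2−p1)² = 31 173.3, rounded up to 31 174.

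Total 2 × 31 174 = 62 348, and 62 348 × 1.1 = 68 583. Both match Table 3. The calculation is one pooled two-proportion test and contains no between-site term.

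**Step 2: power of a pooled or site-stratified common-effect test.** Log RR = ln(26.7/23.2) = 0.1405. Effective births per arm per site are births/(2 × 1.1). The variance of the log RR at a site with n effective births per arm is (1−p1)/(n·p1) + (1−p2)/(n·p2):

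| Site | Effective n per arm | Variance of log RR |
|---|---|---|
| Bandim | 7727 | 0.0102 |
| Matlab | 9545 | 0.0082 |
| Kintampo | 6591 | 0.0119 |
| Dabat | 2591 | 0.0303 |
| IgangaMayuge | 4455 | 0.0176 |

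Inverse-variance pooling gives SE = 0.0504, z = 0.1405/0.0504 = 2.787, and power Φ(2.787 − 1.960) = 79.6%. Simulation gives 79%.

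**Step 3: power of random effects.** Binomial counts were simulated by site and arm (40 000 to 100 000 runs per setting). Site log RRs were drawn around 0.1405 with SD τ, τ² was estimated, and the Wald statistic was compared with 1.96.

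| τ (assumed) | 95% range of site RRs | DerSimonian-Laird or REML | Maximum likelihood |
|---|---|---|---|
| 0 | 1.15 at every site | 71% | 75% |
| 0.05 | 1.04 to 1.27 | 66% | 71% |
| 0.10 | 0.95 to 1.40 | 55% | 61% |
| 0.15 | 0.86 to 1.54 | 44-45% | 50% |

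At τ = 0 the DerSimonian-Laird estimate of τ² was above zero in about 40% of runs, which accounts for the fall from 79% to 71%. With no within-woman clustering (design effect 1.0), DerSimonian-Laird reaches about 75% at τ = 0. Letting baseline SBR differ between sites left the τ = 0 figure at 70-71%.

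**Step 4: births needed.** For 80% power with DerSimonian-Laird, about 1.25 × 68 000 = 85 000 births are needed at τ = 0, and about 1.5 × 68 000 = 102 000 at τ = 0.05. At τ = 0.10, ten times the planned births gives only 82%.

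**The case against.** The strongest answer is that the section itself calls the primary analyses pooled and makes site-specific results secondary; the data sets are to be combined into one multi-site file; and Table 1 lists meta-analysis as one component among descriptive and bivariate analyses. Read that way, the primary analysis and the sample size agree at about 80%. This part stands: the text does not prove that the primary comparison is underpowered, and a reader who infers that as fact goes too far. It does not settle the matter, because the sentence on the overall risk ratio names random effects and nothing else.

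Three further inferences are tempting and not supported.

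- **That 71% is a ceiling.** The article names no variance estimator, and maximum likelihood, or the absence of within-woman clustering, gives about 75%. Still, no variant examined that estimates the between-site variance reached 80%.
- **That 45-55% is the power to expect under modest heterogeneity.** Those figures need an SD of 0.10-0.15 on a log RR of 0.14, so the spread is about as large as the effect.
- **That differing surveillance systems make such heterogeneity likely.** The Discussion calls the systems only slightly different. Surveillance may shift the level of SBR without shifting the ratio between arms. The 3 to 35% range of earlier differences comes from descriptive studies, not from site-level randomised effects.

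A random-effects summary is also a defensible target for a study meant to inform surveys elsewhere. If site effects differ, it and the stratified contrast answer different questions, so the whole gap in power cannot be charged to the estimator.

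**Conclusion.** The point holds as a mismatch between two things that the article states. The 80% is correct for a pooled or site-stratified common-effect test (79-80% at 68 000 births). It is not correct for the only method named for the overall risk ratio. With no heterogeneity at all, the shortfall is about 8 points by DerSimonian-Laird or REML (79% to 71%), or about 4 points by maximum likelihood. The chance of missing a true 15% gain is then about 29% or 25%, against the planned 20%. Larger losses depend on heterogeneity that the article does not quantify: 66%, 55% and about 45% at assumed SDs of 0.05, 0.10 and 0.15.

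The figures rest on the Table 2 sizes being reached, 1:1 allocation, a design effect of 1.1 and a two-sided 5% Wald test. Either reading of the section needs a correction. If the pooled result is the random-effects summary, the power is overstated; if it is something else, the section offers two candidate primary estimates. The severity is moderate.

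**What to change.** In Analysis by objective, name one primary overall estimate of the SBR risk ratio.

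- **Option A, which matches the sample size:** a site-stratified pooled risk ratio from a log-link model with arm and site as terms and the woman as the cluster. Site-specific risk ratios and the random-effects summary become secondary, the latter for generalising beyond these sites.
- **Option B:** keep random effects as primary, and restate the power as about 71% at zero heterogeneity and lower otherwise. Make the change both under Sample size and data collection approach and in the Discussion, and name the variance estimator on which the figure rests.

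Either option changes wording only and needs no new data. The price of Option A is that its estimate speaks for these five selected sites, so the random-effects result must still be reported. The price of Option B is an openly lower power at the planned size.

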## DISCUSSION

The EN-INDEPTH is the first randomised comparison of two survey methods to capture pregnancy outcomes, the current DHS-7 FBH^+^ and FPH. This is a large-scale study (at least 68 000 births) based in five high-burden countries, including one site in South Asia and four sites across West and East Africa. The study is powered to be able to detect a 15% difference in the estimated SBR, but it is also expected to inform our understanding of survey capture of other pregnancy outcomes, notably neonatal deaths, birthweight, gestational age and abortions (spontaneous and induced). Even if the results show a convincing increase in capture of stillbirths or other pregnancy outcomes, a key operational question is whether the FPH takes longer. The software used for our study (Survey Solutions) allows recording of the paradata, including precise timing by section of the questionnaire. This study will, therefore, enable us to conduct more detailed analyses of time spent by question and section, as well as by the fertility context. Underreporting of pregnancy and adverse outcomes may be affected by socio-cultural barriers and survey data collection procedures, so the mixed methods assessment of barriers and enablers to reporting and recording will be valuable.

In addition to omission of events, household surveys are known to have important limitations in the measurement of stillbirths and neonatal deaths, including displacement of reported day of death and misclassification between stillbirths and neonatal deaths [36,37]. Distinguishing between stillbirths and neonatal deaths requires detection of signs of life at birth, notably assessment of heart rate. Recall by a mother in a survey requires her to know whether there were signs of life at birth and for her to report this. Differences in assessment at birth, perceptions of viability, availability of neonatal resuscitation and cultural and religious factors - all potentially have a role in whether a mother will report her baby’s death as a stillbirth or an early neonatal death. This study will examine any differences between reporting of these outcomes in the survey compared to HDSS data, and explore women’s perceptions of stillbirth and neonatal deaths, but will not have the ability to assess “true” stillbirths based on lack of accurate measures of heart rate at birth. Another important misclassification is between early fetal death and late fetal death/stillbirth with a threshold of 28 weeks, based on errors in gestational age measurement and reporting. Again, this study will not have “true” gestational age based on first trimester ultrasound.

Birthweight and gestational age measurements are important from individual, clinical and public health perspectives. From a clinical perspective, they are important to identify liveborn neonates at increased risk of mortality and morbidity, for example, those preterm (born at <37 completed weeks of gestation) or low birthweight (<2500g), to enable provision of extra care [12]. From a classification perspective, this information is critical to differentiate between miscarriages and stillbirths. Studies have shown that data on perceived size at birth recorded in surveys are not consistent with data recorded from health cards and that the quality of recalled birthweight data are variable [38]. In addition, little is known on community perceptions of the importance of birthweight and how this may influence reporting. This study seeks to provide further insights on how to obtain better birthweight data in surveys. Although a gestational age in months is collected in the five-year reproductive calendar in DHS surveys, concerns have been raised regarding the validity of these data. Whilst months are used to differentiate between miscarriages and stillbirths, they are currently not reported in most survey reports and are not used in the estimation of population-level measures, such as preterm birth. In this study, we will assess standard and modified questions that seek to capture gestational age, as well as the internal validity of the reporting of gestational age in months, in weeks, and reported maternal perception of the birth as preterm. In the Matlab site, where more accurate gestational age information is captured in the HDSS through early routine urinary pregnancy testing following a missed period, we will assess the validity of these questions by comparing the information captured in the EN-INDEPTH survey to the HDSS data. This will provide important new information on the feasibility of the use of these questions in household surveys. However, the frequent HDSS household visits might increase women’s awareness of pregnancy duration and improve the reporting of gestational age.

Comparable data on abortion are limited [39]. In countries where abortion is illegal, data are underreported for fear of prosecution or stigma [18]. In contexts where abortion is legal, data may also be problematic. This study will add to the literature by testing the feasibility to asking a small set of abortion questions.

Fertility intentions are subject to substantial variability over time [40]. As part of a multi-country research protocol developed by the “STEP-UP” consortium that the LSHTM is co-leading with the Population Council [33], a set of new questions were developed to improve the measurement of ambivalence. We will test these questions, and because the study is nested in the HDSS sites, we will be able to prospectively assess the link between un-intendedness and pregnancy outcomes. The information collected will support a rigorous assessment of reasons for unmet need for family planning, as well as to assess whether unwanted childbearing is linked to negative pregnancy outcomes.

Registering a child’s birth is a critical first step to protect the rights of every child, and non-registration might prevent the child from accessing health and education services. UNICEF estimates suggest that more than 230 million children under the age of 5 have not had their birth registered [41]. Household surveys represent the largest source of data on birth registration in low- and middle-income countries, [41]. Yet, registration and notification procedures vary, so more research into context specific survey questions is required [42]. In consultation with experts in the Child Protection team in UNICEF HQ, we selected birth registration questions to be evaluated in this study.

Whilst this study has strengths in terms of being randomised for the primary objective, as well as being multi-site and large-scale, pregnancies resulting in a stillbirth are less likely to be captured than those resulting in a live birth, especially if there is no frequent surveillance to capture new pregnancies and live births, even within relatively robust pregnancy surveillance systems. Hence, one limitation of this method is that women with only a stillbirth in the last five years and no live birth would not be surveyed, potentially underestimating the true SBR. In addition, the sites selected for this study have slightly different surveillance systems. Since we are collecting the data in the context of the demographic surveillance system, respondents might already be familiar with these survey questions and may be more likely than women in other settings to report pregnancy losses. If this is the case, we might have a higher reporting of events than in other settings. However, if respondents in the community are indeed more likely to report such events, this should affect women in the HDSS site equally and should not affect the randomised experiment.

The choice of Survey Solutions as our data collection tool might affect comparability with other studies using PAPI or CAPI using the CSPro Windows tablet interface. The main difference between these methods of data collection is that both PAPI and CAPI using the CSPro Windows tablet interface have a roster for the data collection of reproductive histories. In order to minimise such effect, we developed a summary of the reproductive history to mimic the reproductive history roster used in the original PAPI or CAPI using the CSPro Windows tablet application. In addition, another strength of this study is that our customised survey questionnaire developed with Survey Solutions Designer allows the inclusion of interviewer’s instructions and these are visible to the interview for each question as the interviewer progresses during the interviewer visit. This addition might improve data quality.

## CONCLUSIONS

Most of the 5.5 million deaths around the time of birth [1] occur in countries with the least data. Whilst improvement in CRVS and routine facility data systems is crucial, in the meantime the poorest countries rely on household surveys, and equity considerations should drive investment to improve the quality of data capture, especially for the large burden of pregnancy outcomes. We anticipate that the results of this study will inform improved tools and how these tools are applied and enable better measurement of the often-hidden outcomes associated with stigma and suffering of women in many countries. Better data alone will not change these outcomes, but counting and visibility is a crucial first step to change.

## Additional material

Online Supplementary Document
